### Recruitment and planning

Since 1988, the oncogenetics department of Jean Perrin CCC has been collecting pedigree information of cancer-prone families. Today, more than 7000 families are registered in the database, which comprises more than 170,000 members overall. The birthdate and address of counselees are recorded, in addition to the type of cancer risk and various medical annotations (in particular cancer history of the family members).

Individuals meeting the inclusion criteria will be extracted from the database, and invitations will be sent by mail to a randomly selected subgroup of 60 counselees. The first 28 young women answering positively to this invitation will be asked to consult at the oncogenetics department to receive a detailed description of the protocol and sign an informed consent form, by which they will agree to participate in the trial. After their consent is obtained, the participants will be randomized for allocation to the first or second weekend session. They will also receive a training course to enable them to complete the questionnaires using the dedicated website. The overall organization of the trial is displayed in Table 1.

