### Study design

The study is a randomized, prospective, monocenter, psychoeducational phase II trial comparing the evolution of indicators between preintervention and 6 months postintervention. Two groups will be compared: a first group of asymptomatic participants who will attend the session immediately and a second group corresponding to the “waiting list” (control group). The waiting list session will occur 6 months later than that for the first group. Measured indicators will be obtained 2 weeks before and 6 months after the first intervention for all participants, whatever their allocation group (Table 1). This will be possible because the questionnaires will be completed by participants at home on a dedicated website. Groups will therefore be comparable, and the only difference between them will be limited to the intervention.

**Table 1 Tab1:** Schedule of enrollment, interventions, and assessments

		Study period				
	Enrollment and allocation	Baseline values	Session 1	Main outcome values	Session 2	Secondary outcome values
Time points	April-May 2016	First week of June 2016	Third weekend of June 2016	First week of November 2016	Third weekend of November 2016	End of May 2017
Enrollment						
Answer to the invitation letter	X					
Consultation and informed consent	X					
Allocation to session 1 or 2	X					
Website learning	X					
Interventions						
Group session 1			X			
Group session 2					X	
Assessments						
Socioeconomic data	X					
Psychosocial questionnaires		X	X	X	X	X

In March 2016, the study was approved by the local ethics committee (CPP SUD-EST-6: IRB00008526) and registered with ClinicalTrials.gov (NCT02705924).

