#### Data analysis

A statistical analysis plan will be written prior to conducting any outcome analysis, excluding queries to manage data. The statistical analysis will start after the database is locked. This will be done in two steps when the 6-month and then the 12-month questionnaires are collected.

Data analysis will begin with a description of population characteristics (age, known *BRCA* mutation, socioeconomic and educational categories). The balance of these characteristics will be checked by allocation group. Missing data will be analyzed by group, by type of questionnaire, and by time (inclusion, sessions, 6 and 12 months). Further description will present the longitudinal analysis of questionnaire scores over the course of 1 year. Differences related to socioeducational and socioeconomic categorical data and scores at inclusion will be analyzed using one-way analysis of variance (ANOVA) or Kruskal-Wallis H test. Overall convergent/divergent analysis between scores, independently of groups and times, will be verified by correlation analysis (Pearson’s or Spearman’s correlation if distributions are abnormal). A correspondences analysis will present the global description of the results and the relationships between questionnaire dimensions.

The main endpoint will be tested between allocation groups using individual HHI score variations (change at 6 months from time of inclusion) by Student’s *t* test or Mann-Whitney *U* test if normality/homoscedasticity is not achieved. All scores by group will be analyzed longitudinally using two-way ANOVA (mixed model) with either raw scores or their variation from baseline.

The statistical analysis will be performed using SEM software [42] and R version 3.0.1 software. The SPIRIT checklist, describing correspondances between the protocol and standard issues addressed in clinical trial, is provided as Additional file 1.

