## Discussion

Prospective, randomized psychoeducational studies are often difficult to conduct. First, no blinding can be organized; interventions and group allocations are necessarily described in the informed consent form. Second, a particular difficulty is encountered when one tries to precisely define psychological endpoints; they are usually multiple, and they influence each other. Third, some endpoints vary very rapidly shortly after the intervention, but in a labile way, and a quick positive improvement may hide long-term inefficacy. However, developing an intervention without evaluating its effects would lead to a dead end.

To avoid selection bias, randomization using a waiting list is often the best solution. It ensures that participants are alike, and it places them on an equal footing. Unfortunately, if the waiting delay is too long, some of the participants allocated to the waiting list may withdraw for various personal reasons. We do not expect this to happen with our young women; in particular, at such an age, severe diseases are not that frequent, even in an HBOC context. Also, a cost-free stay in a spa center seemed to us attractive enough to limit this possibility. However, we have decided to increase the sample size a little so that such events would not reduce the study’s already limited power (80 %).

The hierarchical structure of our questionnaires is a second difficulty. The tendency to multiply the questionnaires used needs to be fought so that questionnaire completion is acceptable and can be performed in a short time. Especially if the completion has to be repeated over time, the missing data rate can increase, with consequences on estimates. Also, interactions between the various psychosocial dimensions explored cannot be circumvented easily and may induce confusion bias. Special attention must therefore be paid to both the complementarity of questionnaires and the hierarchical validity of studied dimensions. A careful examination of bibliography was performed, and several expert discussions between professional psychologists and methodologists were needed before we reached a consensus.

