Another discussed subject was the “good” time to start evaluating the intervention. The baseline measure was initially placed at inclusion. Because the accrual period will last about 2 months, however, the 6-month delay would not be respected for participants included early. We thus decided to shift the questionnaire self-completion at a fixed time point 2 weeks before the first session for everybody. Meanwhile, as the provision of socioeconomic data at inclusion might be a good opportunity to teach the participants how to use our dedicated website, we decided to reserve a moment after obtaining the consent signature to explain how to enter the site and complete the forms. The evolution of the other estimates and the cross-correlation analysis of questionnaire dimensions will help us to determine if another aspect should be used instead of the focus on “hope” to improve, with better efficacy, the overall QoL of our young women.

Finally, we as yet have no idea how our proposal will be perceived by our young asymptomatic women. The rate of refusal and the reasons by which they will justify their not entering the study will be analyzed and will help us develop better prevention strategies for the youngest counselees. One of the purposes of this phase II trial is to verify the feasibility and acceptability of the intervention to participants, evaluate its effect size on the various scales, and prepare a larger national phase III trial based on a more solid hypothesis. The acceptability is of major importance, and a better definition of the young population that we target may need some adjustments. In particular, the birth of one child does not eliminate worries regarding new procreation projects; perhaps it even increases them as questions about the long-term security of the child (Will I live long enough to ensure his future?) are suddenly raised by his arrival. So, the inclusion criteria of our pilot study will probably need to be widened in a further trial to include young women facing more concretely not only the transmission dilemma of their mutation but also familial existential issues.

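### The baseline hope score is taken after allocation in an open trial, so the primary change score does not rest on a secured pre-allocation baseline

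*Protocol article*

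**What the plan says.** The order of steps is explicit in the protocol article.

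- Recruitment and planning: "After their consent is obtained, the participants will be randomized for allocation to the first or second weekend session".
- Study design, Table 1: the row "Allocation to session 1 or 2" is marked in the enrolment column (April-May 2016). The only assessment in that column is socioeconomic data. The psychosocial questionnaires, which include the HHI, start in the next column, the first week of June 2016.
- Discussion, on how this arose: "The baseline measure was initially placed at inclusion". Accrual was expected to last about 2 months, and the authors continue: "We thus decided to shift the questionnaire self-completion at a fixed time point 2 weeks before the first session for everybody".
- Discussion, on masking: "First, no blinding can be organized; interventions and group allocations are necessarily described in the informed consent form".
- Data analysis: the main endpoint is compared between arms on each woman's HHI change, defined as "change at 6 months from time of inclusion". The Sample size section also starts the change at inclusion.
- Study design, on the result of this scheme: "Groups will therefore be comparable, and the only difference between them will be limited to the intervention".

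**The concern.** In a randomised comparison of change scores, the baseline should be a quantity that the allocation cannot have influenced. Here it comes after allocation. The Discussion justifies the move to a fixed date by the need for an equal interval for everyone. It does not consider that allocation now comes first.

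The endpoint is one that such knowledge could plausibly move. The HHI is self-reported at home. The Objectives section chooses expectations as the first target because they should respond quickly to new information, and the Evaluation criteria section counts them among the labile dimensions. The Discussion relies on the free spa stay being attractive. At the June questionnaire, one arm is two weeks from that stay and the other will wait until November.

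If this difference moves the baseline, subtracting the baseline carries the shift into the primary contrast. The article's claim that the arms differ only by the intervention is then not secured. The trial is small, its test is one-sided, and it is meant to supply the effect size for a phase III trial, so a distortion of a few tenths of an SD would matter.

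**Working it through.** **Inputs.** Sample size section: difference of 1 SD of the HHI change, one-sided alpha 0.05, power 80%, 12 per group, plus 2 per arm for losses, 28 in total. Randomization section: 1:1 allocation. The documents give no size for an allocation-induced shift, so the shift below is an assumption.

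**Reproducing the plan's figure.** The normal-approximation formula is n per arm = 2(z for 0.95 + z for 0.80)² / d². With d = 1 this is 2 × (1.645 + 0.842)² = 12.37. Rounded up this is 13; the plan states 12. At 12 per arm, power is 0.789 by the normal approximation and 0.767 by the noncentral t. At 14 per arm the figures are 0.842 and 0.824. The two-sided version would need 16 per arm, so the stated figure comes from the one-sided formula.

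**How a baseline shift enters.** Let knowledge of the allocation move mean baseline hope by s1 in the session 1 arm and by s0 in the waiting-list arm, both in SD of the change score. Let b = s1 − s0, and suppose follow-up scores are unaffected. Then

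expected observed difference in change = true difference − b.

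A lift in the session 1 arm and a drop in the waiting-list arm both make b positive, which shrinks the contrast. A negative b, for example from apprehension before session 1, enlarges it.

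**Power when b is positive and the true effect is 1 SD.** One-sided two-sample t-test, df = 2n − 2, noncentrality = (1 − b)√(n/2):

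| b (assumed) | effect seen | power, 12 per arm | power, 14 per arm |
|---|---|---|---|
| 0 | 1.0 | 0.767 | 0.824 |
| 0.1 | 0.9 | 0.688 | 0.750 |
| 0.2 | 0.8 | 0.600 | 0.661 |
| 0.3 | 0.7 | 0.507 | 0.563 |

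**Type I error when the true effect is zero.** Same test, noncentrality = −b√(n/2). With b = −0.1 the rejection probability is 0.080 at 12 per arm and 0.083 at 14. With b = −0.2 it is 0.121 and 0.129. With positive b the test becomes conservative: 0.030 at b = 0.1 and 0.017 at b = 0.2, at 12 per arm.

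**The reference point.** Data analysis and Sample size start the change at inclusion. Table 1 collects no psychosocial questionnaire at enrolment, and the Discussion says the baseline was moved away from inclusion. The two descriptions do not name the same time point.

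**The case against.** Several points on the other side have weight.

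- **Disclosure is not stated.** No section says when each woman learns her session. The consent form describes the two groups as part of the design, which is not the same as telling a woman her own allocation. Notification may be set out in the full protocol. This stands as a limit on certainty. The inference is still strong, because the article says "no blinding can be organized", the allocation is a date for a residential weekend, and the baseline falls two weeks before the first one.
- **Baseline still precedes the intervention in both arms, and the fixed date has a sound purpose.** Both are true. The weakness is the order relative to allocation, and the fixed date can be kept.
- **The likely direction is conservative.** Pleasure at an early place, or disappointment at waiting, would count against the intervention. That is fair. It still costs power and biases the effect estimate that phase III would use.
- **The inclusion wording is a label.** The Data management and Data analysis sections use inclusion as the name of the first questionnaire time point. This is an editorial correction and adds nothing to the bias argument.

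A reader might go further in two ways that the article does not support. First, one might count anticipation twice, because the waiting-list arm gives its main outcome about two weeks before its own session. That lift would arise even with a perfect pre-allocation baseline, so it is a separate limitation. Second, one might call the one-factor minimisation predictable. The invited women are a random selection, the first 28 positive replies are taken, and consent precedes randomisation, so prediction has little to act on. Any random element in the minimisation is detail that an article may omit.

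**Conclusion.** The point holds as a weakness in the order of steps. The article places allocation before the first HHI and subtracts that HHI in the primary test. Nothing in it keeps the allocation from the women in between, so its statement that the arms differ only by the intervention is not secured for the change score.

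The conclusion rests on the strong but unstated inference that women know their session in early June, and on an assumed shift. For 0.1 to 0.2 SD against the intervention, the loss is about 8 to 17 percentage points of power at 12 per arm (0.77 to 0.69 or 0.60) and about 7 to 16 at 14 per arm (0.82 to 0.75 or 0.66). A shift in favour would raise the one-sided type I error above 5%. A reader might infer that the trial has an inflated false-positive rate, but the documents do not show this, because they support neither that direction nor any particular size. The point shows that a route for bias is open and can be closed cheaply. It does not show that the result will be biased.

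**What to change.** Either of two changes closes the route. Both leave 12 per group, 28 in total and alpha unchanged.

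1. Keep consent and website training in April-May and the fixed June baseline, but generate or disclose the allocation only after each woman's baseline questionnaires are submitted and locked. Ask all women to hold both weekend dates. The cost is less than two weeks' notice of session 1, in a trial that already allows for last-minute refusals.
2. Collect the HHI at the consent and website-training visit, before allocation, and use it as the primary baseline. The cost is one more short (12-item) questionnaire if the June one is kept, and a baseline-to-outcome interval that varies by up to about 2 months, which is the variation the authors wanted to avoid.

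In either case, align the inclusion wording in the Data analysis and Sample size sections with the baseline actually used. If the full protocol already withholds allocation until the baseline is complete, say so in the article.

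If allocation has already been made and disclosed, add a sensitivity comparison of the 6-month HHI scores that does not use the post-allocation baseline. It avoids the baseline shift. With equal variances σ² at both times and correlation ρ, the variance of change is 2σ²(1 − ρ), so the raw 6-month comparison is less precise than the change score when ρ exceeds 0.5.

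None of these steps removes anticipation in the waiting-list arm before session 2. That should be acknowledged as a separate limitation.

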### Randomization

Participants will be randomized 1:1 to the first or second session (intersession delay = 6 months) using a minimization technique and stratified according to the existence or absence of a familial *BRCA* mutation. We assumed that this characteristic might induce variations in coping and expectations and thus alter the impact of the psychoeducational intervention if the studied population were not balanced with regard to this characteristic.

### Evaluation criteria

Endpoints and their evolution will be evaluated using self-questionnaires. To obtain relevant data, these questionnaires needed to match several criteria:Expectations, personality traits and coping strategies likely correlate, so a hierarchy between these psychosocial variables was necessary to prioritize our objectives. Many questionnaires could have been selected for investigation of the relevant psychological dimensions, but their number had to be limited to the necessary minimum so that the time for questionnaire completion would not take too much time and the rate of missing data would be acceptable.Because they are too young, participants that we accrue do not naturally focus on cancer and other health issues. We thus wanted to avoid as much as possible questionnaires that target mainly health domains.Questionnaires had to be validated and translated into French.

Figure 1 depicts the construct of our psychological model and the questionnaires used at each level.

**Fig. 1 Fig1:**
[figure not shown]
Construct of the psychological model enabling the evaluation of the study endpoints. *HHI* Herth Hope Index, *IPC* Internal, Powerful Others, and Chance Locus of Control Scales, *QoL* Quality of life, *SES* Self-Esteem Scale, *STAI* State-Trait Anxiety Inventory, *WCC* Ways of Coping Checklist, *WHOQOL* World Health Organization Quality of Life questionnaire

The various endpoints evaluated in our protocol start from personality traits characterizing our young counselees that can be considered stable: self-esteem and trait anxiety belong to this category. We rejected any characterization of other general personality traits and/or psychiatric disorders, considering that such topics, too distant from our objectives, should be of limited influence on our endpoints (because of the study selection criteria) and would provide variables with too large a range of categories that our study would not efficiently handle (too small a sample size).

Two questionnaires evaluate personality traits: the Self-Esteem Scale (SES) [9] and the State-Trait Anxiety Inventory (STAI)-B for the rather stable anxiety trait [10, 11]. At the second level, coping is examined using the Ways of Coping Checklist (WCC), the ways of coping described by Folkman and Lazarus [12, 13]. Resulting from interactions and feedback between the individual and the environment, perceived control is a pivotal concept. Levenson [14] has shown that it has three aspects: a locus of control originating in the self, and another one located outside the individual with two possible sources: fate/luck and “powerful others.” For our counselees, we might wonder if HBOC predisposition is considered an inner or outer locus and if an unknown mutation could boost the “fate/chance” dimension. In young women, the locus of control may influence two further labile dimensions: anxiety (state) on the one hand, and expectations on the other. We will evaluate state anxiety using the STAI-A, while expectations will be explored with the Herth Hope Index (HHI) [15, 16]. The overall outcome of this construct in interaction with standard education and/or socioeconomic levels will be estimated using the World Health Organization Quality of Life (WHOQOL) generalist questionnaire [17]. All of these questionnaires are detailed below.

#### Herth Hope Index

With the HHI [15, 16], expectations can be split into two “spheres” [18]: first a factual, concrete level; second, a subjective one that includes optimism/pessimism, confidence, and the feeling that life makes sense. The first sphere includes the possible evolution of science that will perhaps someday discover remedies against cancers and genetic predispositions. We did not plan to investigate this sphere on which individuals have no influence. The second sphere is more interesting for our purposes: We expect that with adequate and positive information, the confidence in the future of our young women will grow and that they will be able to build projects more easily. Rustøen et al. [19] reported that, among newly diagnosed cancer patients, hope could be improved by using a short psychoeducational intervention, although the improvement for their patients did not persist 6 months later, nor did it seem to influence QoL. Our hypothesis is that such persistence in asymptomatic young adults may last 6 months or more, and this is our main endpoint.

The HHI fits this second sphere of expectations. It has demonstrated very good psychometric qualities, in particular among cancer patients, among whom hope appears to be a basic mechanism involved in coping [16]. Phillips-Salimi et al. [20] proved the validity of the HHI in adolescents and young adults with cancer. We think it is well adapted to our young participants in particular because it is not health-oriented; it will not echo in young women with HBOC a future possible disease and therefore will not risk stressing them uselessly. In a different domain, hope management has demonstrated some efficacy in the prognosis of cardiovascular disease [21]. This conclusion let the authors propose a five-step management plan to maintain hope within a transition framework: (1) acknowledging the changing of life circumstances, (2) restructuring reality, (3) dealing with vulnerability, (4) achieving normalization, and (5) resolving uncertainty” [22]. Our intervention will deal with the four last steps.

Another advantage of the HHI is its short format: It contains only 12 simple proposals quoted using a 4-point Likert scale, ranking from 1 = strongly disagree to 4 = strongly agree. Its internal structure is composed of three dimensions: temporality and future, positive readiness and expectancy, and social/spiritual connectedness [23]. Although we expect that our intervention may improve preferentially the first two dimensions, the global score will constitute our primary endpoint (sum of all 12 items, but items 3 and 6 reversed). This questionnaire has been translated and validated in French by Lafrance [24]. It will be used to evaluate the primary endpoint; the other questionnaires described below will be used to evaluate secondary endpoints.

